## Methods

### Study Design

In Phase 1 of the study we will: (1) complete a qualitative study of critical chronic disease management skills and knowledge with key informants and patients, (2) use the results of the qualitative study to inform the development of a tailored computer-delivered CDSM health literacy intervention, and (3) complete acceptability and usability testing of the tablet-delivered version of FLIGHT/VIDAS and the intervention. In Phase 2, we will complete a clinical trial of the effects of the new intervention on multiple outcome measures.

### Phase 1

During the qualitative procedures in Phase 1, individual interviews will be completed with at least 20-30 individuals with a chronic disease (at least one chronic condition from planned inclusion criteria for Phase 2; sampling will continue until saturation is reached). Purposive sampling will be employed so that age, gender, race, language, and chronic conditions are adequately represented. During an earlier study, participants completed a questionnaire asking whether they had been diagnosed with specific health conditions. Results from this questionnaire will be used to recruit these same persons for Phase 1 procedures, based on the specific health conditions that were reported earlier. We will target individuals with a variety of conditions, as well as those with multiple conditions.

Interviews will be conducted in English or Spanish at Nova Southeastern University in Fort Lauderdale, Florida and at Emory University in Atlanta, Georgia, and information will be digitally recorded and transcribed for subsequent analyses. In-depth interviews will also be completed with 10 key informants (5 English-speaking and 5 Spanish-speaking) selected from diverse disciplines, who are familiar with the treatment of chronic illnesses, including: geriatric, internal, and family medicine; nursing; and social work. Interviews will be open-ended but will be semistructured to make it possible to elicit informants’ input on each of the key problems in chronic disease management that span across conditions. These problems include: fatigue, pain or physical discomfort, shortness of breath, sleep problems, depression, anger, stress, memory problems, and adherence.

After preliminary analyses, four focus groups will be completed (28 total participants, with one group in Spanish) with participants who are also representative of potential consumers of the intervention, to provide checks on concordance and trustworthiness of the themes identified in interviews. During these focus group sessions, we will solicit suggestions that more accurately represent the life situations of our study population.

Although interviews will cover the same material, interview content will be tailored to each participant's unique situation. Within each area, there will be several subareas designed to further understand these phenomena. We will use NVivo for Windows, Version 10 (Melbourne, Australia: QSR International) to assist in coding data, searching text, and conducting cross-case analyses. An inductive thematic analysis will be used, as this technique allows for the patterns, themes, and categories of analysis to emerge [58]. The software allows for a process that incorporates an emic approach to analysis, and allows for an exploration of indigenous concepts and typologies. The study design will allow for a consideration of the credibility of themes elicited in individual interviews by cross-checking them with focus group participants and key informants. In the final part of Phase 1, content modules will be refined and modified, based on this iterative process and using data from the interviews.

Intervention materials focusing on behavioral self-management skills will be created for each problem area (eg, exercise and self-guided cognitive behavioral interventions for pain [59], meditation for stress [60], behavioral activation for depression [61,62], cognitive behavioral interventions for sleep disturbances [63], and our own model for treatment adherence [29,38]). All key problems in chronic disease management listed above will be assessed by measures in our battery at baseline and all follow-ups, allowing for direct evaluation of the intervention’s effects on specific CDSM problems.

#### Interventions

Information from this qualitative phase will lay the basis for developing general content modules that are consistent with the ASK model of health literacy [26]. This process will draw specific content from established domains of chronic disease management by teaching health literacy skills and health condition conceptual knowledge.

Interventions will be developed that are consistent with recommended strategies for persons with limited literacy skills [64,65]. All materials will use health care-related content as a vehicle (eg, prose about diseases or a table about desirable blood sugars). Intervention elements will focus on the three basic literacy types, as defined by the Educational Testing Service: prose, document, and quantitative [66]. Consistent with research on the effectiveness of direct training in reading comprehension for adult learners [67], training in prose comprehension will focus on strategies to develop functional skills such as identifying key facts, inductive reasoning from multiple facts, and self-monitoring of comprehension. Training in document literacy will use tables, charts, and health-related forms (eg, insurance, consent) and emphasize strategies for identifying key information and strategies for using the information to answer relevant questions (eg, “Which insurance program is better for me?”). Training for quantitative skills will integrate basic instruction on quantitative concepts and procedures for understanding risk, probability, and cost [68,69].

#### Content

Information from the qualitative phase will allow us to develop general content modules that will focus on the key problems in chronic disease management listed above. Key strategies will be to teach health literacy skills and improve health condition-related knowledge. Problems, needed and useful skills, and disease-related conceptual knowledge revealed in qualitative work will then be used by investigators to create a content outline for each module. Content-relevant skills will be integrated with condition-related knowledge in each module (eg, by teaching reading comprehension skills using materials that are directly related to health). We will use a similar strategy in teaching listening comprehension by focusing on encounters with healthcare providers. This might involve teaching strategies for preparing a list of questions before an appointment, taking notes during the encounter, and being appropriately assertive in interactions.

Cognitive load theory [70,71] dictates that for optimal learning, instructional material must be presented in segments of content that do not exceed the learner’s ability to take in and retain each element. Consideration of this issue may be especially important in persons with limited health literacy [72]. Consistent with this issue, material will be presented in small segments via text and audio, with graphic elements reinforcing themes but not distracting from participants’ learning [70]. Interactions with the computer will only require that participants tap on the screen to press images of buttons, thereby keeping required computer skills to a minimum.

In a series of team meetings, content created by individual team members will be reviewed and alternate versions will be created at the three reading levels planned for each intervention group (3^rd^, 6^th^, and 8^th^ grade levels) based on the Flesch-Kincaid formula for English [73] and its Fernandez-Huerta modification for Spanish [74]. No clear criterion for the difficulty of health-related materials is available for use in tailoring, so we will use the criterion of grade equivalent levels. In this context, however, it will measure the difficulty of *health-related* materials and thus materials will be tailored to participants’ levels of health literacy.

Intervention content will be developed in either English or Spanish, with versions translated by team members fluent in the target language, with an emphasis on appropriate cultural adaptation rather than literal translation [75]. This strategy was previously effective in creating a health literacy measure in both English and Spanish [25], and helped to ensure that both language versions were intelligible to individuals from diverse linguistic and cultural backgrounds. Given the importance of regional usages of Spanish (eg, the same word may mean different things in Puerto Rico or Mexico), the Spanish version will be developed with an emphasis on standard Spanish to avoid comprehension problems. Intervention content will be assessed during usability testing, in addition to a focus on interface design and ease of use.

#### Usability Testing

After creation, acceptability and usability testing of the new materials will be completed using a procedure that we successfully used in other projects [76,77]. Individuals will be observed interacting with the computer app and will be asked to *think out loud* [78] so that their cognitive processes can be tracked, and areas of difficulty can be identified [76]. After five participants have completed this process, the intervention will be revised and tested again with a new group of five participants [77]. This process will be repeated until no further difficulties are identified, potentially eliciting responses from 15 to 20 participants [79,80].

#### Technology

Implementation will allow participants to monitor their own progress and provide centralized data collection. The intervention will be created in standard off-the-shelf software, *Captivate* (Adobe Corporation; San Jose, California), which is widely used in developing educational media. This software has been used in previous projects due to its ease of use, integration of multimedia elements, and simple deployment to most learning management systems. The current version (*Captivate 9*) creates apps in HTML5/CSS/JavaScript formats that can be readily deployed on Windows, iOS, and Android devices, and on the Internet. Output from this program can be readily packaged as downloadable apps for the operating systems of most mobile devices, including iOS (iPhone, iPad), Android, and Windows Phone.

#### Tablet Computer Adaptation

Delivery of FLIGHT/VIDAS on tablet computers will require modifications to the size of graphics, layout of page elements, and changes in font sizes. The file size for graphic elements will be reduced to improve download times over the Internet. Studies continue to show a dramatic increase in Internet use among older persons [81] and multiple studies show that elders evaluate the usability of tablet computers positively [82-84]. We will ask all participants to complete FLIGHT/VIDAS and the health literacy intervention on tablet computers, but it is possible that some of the oldest participants may not be able to do so. All participants in our previous study were able to complete assessments on touch screen computers (94 of whom were 70 years of age or older), so participants who have difficulty (ie, express frustration or state that they are not able to accurately record responses) with tablet computers will use the larger-format touch screen.

### Phase 2

#### Participants

We will recruit Spanish- and English-speaking persons aged 40 years and older whose health literacy is at the 8^th^ grade level or lower. Literacy levels will be assessed via validated scores on the Rapid Estimate of Adult Literacy in Medicine (REALM) [85], or the Short Assessment of Health Literacy in Spanish Speaking Adults (SAHLSA) [86]. This level was chosen to include persons in the lower end of the basic proficiency level and below, as defined by the US National Assessment of Adult Literacy [1,87-89]. The REALM and SAHLSA were selected based on their demonstrated relation to health status in other studies and data from our previous study that enabled us to use them as screening tools. The intervention will thus target those most likely to profit from instruction at a moderate difficulty level approximately two grade levels lower than this (6^th^ grade), or those who may need low-literacy level instruction (3^rd^ grade) based on their instructional reading level being approximately two grade equivalents below the tested level. English-speaking participants will include approximately equal numbers of African-Americans and non-Hispanic whites, with recruitment stratified by age decades (to enhance existing FLIGHT/VIDAS norms) from age 40, with no upper limit. Considering the importance of broadening the geographic basis of our normative population and ensuring the usefulness of the health literacy intervention for diverse groups, in the proposed study we will expand data collection to include Grady Memorial Hospital in cooperation with our collaborators at the Morehouse School of Medicine and Emory University (all in Atlanta, Georgia). We will continue to recruit African-American, white non-Hispanic and Hispanic participants at our Nova Southeastern University site, as we did in our earlier project. During this project, we plan to expand our recruiting efforts in South Florida to include larger numbers of Spanish speakers with low educational backgrounds who are originally from Mexico. We will randomize 432 participants, as needed (216 at each site; see power analyses for sample size justification, below). Numbers of participants in Figure 1 reflect planned recruitment based on power analysis and potential attrition.

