### Aims and Hypotheses

In Aim 1 we will adapt and evaluate the tablet computer-administered measure of health literacy developed during an earlier study with African-American, Hispanic, and white non-Hispanic individuals 40 years of age and older, which operated on tablet computers. The two hypotheses of Aim 1 are: (*Hypothesis 1*) alternate forms of the new health literacy measure’s general health literacy and numeracy scales will be sensitive to intervention effects, showing improvements after participants complete the intervention; and (*Hypothesis 2*) the new health literacy measure will be acceptable, usable, and valid when administered on tablet computers.

In Aim 2 we will use the computer-administered measure to assign participants to a racially- and ethnically-tailored intervention that is delivered in a way that is appropriate to their level of health literacy. The two hypotheses of Aim 2 are: (*Hypothesis 3*) an interactive multimedia intervention will be more effective in improving health literacy, self-reported health, patient activation, health self-efficacy, and treatment adherence compared to a matched active control intervention; and (*Hypothesis 4*) the interactive multimedia intervention tailored to participants’ characteristics will significantly reduce health literacy differences between white non-Hispanics, African-Americans, and Hispanics.

In Aim 3 we will assess mediators and moderators of the relation of health literacy to race and ethnicity. We will also explore how these mediators and moderators are linked to health behaviors and actual health outcomes. The two hypotheses of Aim 2 are: (*Hypothesis 5*) health literacy will mediate relations between age, race and ethnicity, socioeconomic status, cognition, academic skills, and health status; and (*Hypothesis 6*) health literacy will moderate response to the health literacy intervention, with blacks and Hispanics with lower initial levels showing a greater response to the intervention than white non-Hispanics with higher levels of health literacy.

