### Treatment Assignment

#### Inclusion and Exclusion Criteria

Participants will be eligible for the study if they are 40 years of age or older, are treated for at least one of the conditions in the Functional Comorbidity Index [90] (cardiovascular disease, arthritis, cancer, lung disease, osteoporosis, depression, and others) with at least one medication, have health literacy below the 8^th^ grade level as indicated by the REALM (English) or SAHLSA (Spanish), and are willing to participate for the length of the study. Potential participants will be excluded if they are not able to provide informed consent, have a cognitive or psychiatric disorder that impairs their ability to safely participate in the study, or are not able to remain involved over the full length of the study.

A screening procedure for the new project was developed by assessing the ability of the REALM [85] or SAHLSA [91] to predict if participants had an 8^th^ grade or lower level of reading on the Woodcock-Johnson or Muñoz reading tests. Using the R statistical package pROC [92], a score of 62 on the REALM predicted reading skills less than an 8^th^ grade level on the Woodcock-Johnson (area under the curve [AUC]=0.79, 95% CI 0.72-0.87; sensitivity=0.80, specificity=0.67) with similar results for the SAHLSA. Earlier analyses showed that the FLIGHT/VIDAS General Health Literacy (HL) scale will also be effective for use in detecting participants with lower levels of reading skills (all *P-* values <.001). Analyses did not differ for language groups (AUC for Spanish sample=0.86, *P*<.001).

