#### Recruitment and Retention

Recruitment at the Atlanta sites will take place in the Primary Care clinics of Grady Health Services and Emory Healthcare. Grady Health Services is the largest public health provider in Georgia, and fifth largest in the nation, with more than 130,000 outpatient visits per year. Emory Healthcare has satellite clinics throughout metro-Atlanta and serves a broad array of patient demographics and backgrounds. In current studies, it is possible to access the electronic medical record to prescreen study participants. We will continue this practice after obtaining Institutional Review Board (IRB) permission. The study recruiter will identify potential participants meeting inclusion criteria; he or she will then meet with clinic staff and providers, supply them with study information (flyers, brochures), and ask the clinic staff/provider to give the study information to these potential participants. Passive recruitment through study flyers and information about the study on clinic phone-wait systems will also be used. All studies utilizing these procedures are currently on target with recruitment goals.

In addition to a pool of subjects who participated in prior studies and have given permission to contact them in future studies, Spanish-speaking Hispanics will be recruited from Nova Southeastern University internal, family, and geriatric medicine clinics. Special efforts will be made to recruit a diverse group of Hispanics representative of South Florida and the rest of country’s Hispanic population, per US census data, particularly with respect to country of reference and educational attainment. In our previous study, we recruited more than 320 Spanish-speaking Hispanics over 3 years of active recruitment [25-28].

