#### Study Hypotheses

Hypotheses will be tested via three aims, detailed below.

##### Aim 1

*Hypothesis 1* regarding the sensitivity of alternate forms of the health literacy measure to the intervention will be tested by calculating the simple sum of the HL and NUM scales for baseline (Form A) and first follow-up (Form B), and test their difference via paired *t*-tests, since this is a straightforward strategy that might be used in research and clinical work. This hypothesis will also be evaluated using a mixed-effects regression model with repeated measures for all three assessments that will include relevant covariates such as race/ethnicity, age, education, and cognition. Models for completers and intent-to-treat groups will be created. *Hypothesis 2*, regarding the validity of the measure on tablet computers, will be assessed by evaluating item difficulties and discriminations, calculation of scales’ internal reliabilities (Cronbach alpha), evaluation of construct validity via examination of the measure’s factor structure, and evaluation of concurrent validity as correlations and partial correlations of FLIGHT/VIDAS scales with other measures (Test of Functional Health Literacy in Adults, REALM, and SAHLSA). Measures of scale characteristics (mean, standard deviation, Cronbach alpha, and correlations with other measures) will be compared to values obtained for the full-size computer administration obtained during an earlier study [25] using tests for differences in means, standard deviations, and correlations.

##### Aim 2

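### Hispanic ethnicity is largely, possibly completely, confounded with test language, and no stated analysis separates them, so Hispanic level differences in health literacy cannot be read as ethnic differences alone

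*Protocol article*

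**What the plan says.** All places are in the protocol article.

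- **Who is recruited in which language.** Participants says "English-speaking participants will include approximately equal numbers of African-Americans and non-Hispanic whites". Recruitment and Retention says "Spanish-speaking Hispanics will be recruited from Nova Southeastern University internal, family, and geriatric medicine clinics". Participants also says "We will continue to recruit African-American, white non-Hispanic and Hispanic participants at our Nova Southeastern University site", without naming a language.
- **What language determines.** Under Inclusion and Exclusion Criteria, participants must "have health literacy below the 8^th^ grade level as indicated by the REALM (English) or SAHLSA (Spanish"), so the screen follows the language. Under Content, the health literacy measure is said to exist in English and Spanish, made with an emphasis on cultural adaptation over literal translation.
- **What supports comparability.** Inclusion and Exclusion Criteria reports that the REALM predicts reading below 8th grade on the Woodcock-Johnson (AUC 0.79), with similar results for the SAHLSA. After a sentence on the FLIGHT/VIDAS General Health Literacy scale it adds "Analyses did not differ for language groups" (Spanish AUC 0.86, P<.001).
- **What is compared.** Hypothesis 4 concerns reducing health literacy differences among the three racial/ethnic groups. Hypothesis 5 states that "health literacy will mediate relations between age, race and ethnicity, socioeconomic status, cognition, academic skills, and health status".
- **What psychometric work is planned.** For Hypothesis 2, Study Hypotheses lists item difficulties and discriminations, internal reliability, "evaluation of construct validity via examination of the" measure's factor structure, and correlations with other tests. The scale characteristics are then compared with those from the earlier full-size computer version. Language is not among the example covariates given for the Hypothesis 1 model.

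**The concern.** If nearly all Hispanic participants are tested in Spanish and everyone else in English, a Hispanic versus non-Hispanic difference in scores has two possible sources: literacy, and the test version. The psychometric tools that could tell them apart are in the plan, but the comparison they are explicitly aimed at is tablet versus full-size computer, not English versus Spanish. Hypotheses 4 and 5 nevertheless compare scores across the language boundary.

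What is at stake is the reading of Aim 3. If one version is harder, that difference would be reported as an ethnic difference in health literacy and carried into the mediated effect on health status. It could exaggerate a gap or hide one.

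**Working it through.** **1. The plan's own sample size.** Power Analyses gives 30 completers per cell, three conditions by three racial/ethnic groups, with up to 38% attrition. 30/(1 - 0.38) = 48.4, rounded up to 49; 49 × 9 = 441. Conversely 432/9 = 48 and 48 × 0.62 = 29.8, about 30. The planned 432 is reproduced and is not in dispute. The cells contain no language factor.

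**2. Can ethnicity and language be separated?** Assume 432/3 = 144 per racial/ethnic group at baseline (Figure 1 is not shown) and SD 1. Fit an intercept, an African-American indicator, a Hispanic indicator and a Spanish-version indicator.

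- If no Hispanic is tested in English, the Hispanic and Spanish columns are identical: rank 3 of 4, not separable.
- If k Hispanics are tested in English, the language-adjusted Hispanic-white contrast rests on those k people: SE = sqrt(1/144 + 1/k), against sqrt(2/144) = 0.118 unadjusted. The variance ratio is (1 + 144/k)/2.

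| Assumed English-speaking share of Hispanics | k | SE (SD units) | Variance ratio |
|---|---|---|---|
| 5% | 7 | 0.39 | 10.8 |
| 10% | 14 | 0.28 | 5.6 |
| 20% | 29 | 0.20 | 3.0 |
| 30% | 43 | 0.17 | 2.2 |
| 50% | 72 | 0.14 | 1.5 |

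The African-American versus white SE is 0.118 in every row, because both groups are tested in English.

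**3. Effect of a constant version shift on levels.** Let all Hispanics be tested in Spanish and let the Spanish version move scores by s. The observed Hispanic-white gap is the true gap plus s. With a true gap of 0 and an assumed s = 0.3 SD, the observed gap is 0.3 SD, or 0.3/0.118 = 2.5 standard errors.

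In the mediation model, write a for the ethnicity-to-literacy path and b for literacy-to-health. The shift turns a into a + s. The indirect effect becomes (a + s)b and the direct effect falls by sb, so the total is unchanged but its split is wrong. The relative distortion is s/a in size:

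- true a = 0.5 SD: 0.1/0.5 = 20% to 0.3/0.5 = 60%
- true a = 0.3 SD: 0.1/0.3 = 33% to 0.3/0.3 = 100%

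**4. Effect of a constant shift on the randomized test.** The gap-reduction test compares change by arm between ethnic groups. The shift s is present before and after and in both arms, so it subtracts out: a true contrast of 0.0 is recovered as 0.0, and 0.4 as 0.4.

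**5. Effect of unequal scaling.** If Spanish scores respond at an assumed 0.8 of the English rate, a true arm effect of 0.5 SD shows as 0.5 × 0.8 = 0.4 SD in Hispanics, a false arm-by-ethnicity difference of 0.10 SD. If the arm effect is zero, no false interaction arises. With 30 completers per cell, 60 tailored and 30 control per ethnic group, the SE of that difference is sqrt(2 × (1/60 + 1/30)) = 0.32 SD. Assuming a baseline correlation of 0.7, it is 0.32 × sqrt(1 - 0.49) = 0.23 SD. The artefact is under half a standard error.

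**6. Does the reported AUC settle the matter?** An AUC computed within one language depends only on ranks. Adding any constant to all Spanish scores leaves it unchanged, so it cannot show that score levels agree. The criterion test also differs by language (Woodcock-Johnson or Muñoz).

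**The case against.** The strongest reply is that the document nowhere says that every Hispanic will be a Spanish speaker. A reader might infer that ethnicity and language are fully aliased. The text does not support that: the sentence on English speakers says whom they include, not whom they exclude; Hispanics at the Nova site are also named without a language; eligibility has no language-by-ethnicity rule; and Interventions lists preferred language separately from racial or ethnic relevance. This stands, which is why the point is put as largely, possibly completely. It does not remove the problem: step 2 shows that a small English-speaking share separates the two only imprecisely, and no such adjustment is stated.

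A reader might also take the Spanish AUC as the only evidence on comparability. It is not. It follows a sentence on the General Health Literacy scale and most naturally refers to it, while the screens have their own statement of similar results for the SAHLSA. Both concern prediction within a language, so neither answers the question about levels.

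A reader might conclude that Hypothesis 4 as a whole, or every racial comparison, is compromised. That goes too far. The African-American versus white contrast is within English, and a constant shift cancels in the gap-reduction test. Only unequal scaling or responsiveness could bias that test, and only for the Hispanic comparisons.

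Finally, the earlier development studies may have examined English and Spanish item functioning, and analysis by language may sit in a fuller plan. Neither can be known from this article. But the article does specify the Hypothesis 2 comparison in some detail, and directs it at delivery mode.

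**Conclusion.** The point holds for Hispanic versus non-Hispanic differences in level: the Hispanic-to-literacy path and indirect effect in Hypothesis 5, and the descriptive baseline gap behind Hypothesis 4. As planned, these combine ethnicity with language, screening test and test version, and nothing stated takes them apart.

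The size of any version difference is unknown. The 20 to 100% distortion rests on assumed shifts of 0.1 to 0.3 SD and assumed true paths of 0.3 to 0.5 SD; the precision figures rest on an assumed 144 per group. What does not depend on those values is that a constant shift enters the level contrast in full, leaves the African-American versus white contrast alone, and drops out of the randomized gap-reduction test. The possible scaling bias in that test is secondary: 0.10 SD under the assumed 0.8 ratio, small against its standard error. This limits what Aim 3 can conclude about Hispanics; it does not undermine the trial's randomized comparison.

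**What to change.** - State whether English-speaking Hispanics will be enrolled and, if so, about how many.
- Add to the Hypothesis 2 analyses a two-group (English, Spanish) differential-item-functioning or measurement-invariance analysis of the baseline HL and NUM scales in MPlus. Form A is given to everyone before randomization, so no new data are needed.
- Keep the simple-sum score as planned. Repeat the Hispanic contrasts in Hypotheses 4 and 5 with anchored or partially invariant scores as a sensitivity analysis. Replacing the planned score outright would break the link to the existing norms and to the earlier study's values.
- Report the African-American versus white contrast separately, as the within-language race result.
- Label the Hispanic level contrast as ethnicity and language combined, unless invariance is shown or enough English-speaking Hispanics are enrolled to separate the two.

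The cost is a little more analysis with software already planned, and a narrower claim about Hispanic ethnicity. One limit should be stated with the results: an invariance analysis needs some items that work alike in both languages, and a shift common to every item would look the same as a true difference in literacy.
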